## Abstract

**Background:**

Conducting randomized controlled trials on traditional Chinese non-drug therapies has been limited by factors such as patient preference to specific treatment modality. The aim of this study is to investigate the feasibility of applying a partially randomized patient preference (PRPP) trial model in evaluating the efficacy of two types of traditional Chinese medicine therapies, acupuncture and cupping, for fibromyalgia while accounting for patients’ preference of either therapeutic modality.

**Methods:**

This protocol was approved by the Institutional Ethics Committee of affiliated Dongfang Hospital, Beijing University of Chinese Medicine (approval number: 2013052104-2). One hundred participants with fibromyalgia will be included in this study. Diagnosis of fibromyalgia will be based on the American College of Rheumatology criteria. Before treatment, participants will be interviewed for their preference toward acupuncture or cupping therapy. Fifty participants with no preference will be randomly assigned to one of the two groups and another 50 participants with strong preference to either acupuncture or cupping will receive what they choose. For acupuncture and cupping therapy, the main acupoints used will be tender points (*Ashi).* Treatment will be three times a week for 5 consecutive weeks with a follow-up period of 12 weeks. Outcome measures will be qualitative (patient expectation and satisfaction) and quantitative (pain intensity, quality of life, depression assessment).

**Trial registration number:**

NCT01869712 (in clinicaltrials.gov, on 22nd May 2013).

## Background

In the last two decades, randomized controlled trials (RCTs) have been used to evaluate the efficacy of traditional Chinese medicine (TCM) therapies. In most cases, these trials have investigated herbal drugs [1]. However, limitations exist when conducting RCTs for non-herbal therapies such as acupuncture, cupping therapy, and moxibustion. Therapeutic effects can be influenced by factors other than the efficacy of the interventions themselves;such actors may include patient preference, practitioner preference, and patient-practitioner relationship, among others [2]. Based on the design principle of RCTs, participants are precluded from making their own choices during allocation to the intervention or control arms to avoid performance bias due to strong preference of participants who are not blinded during the trial. Unfortunately, there is no ideal placebo control for most types of non-drug therapies, which means successful blinding is almost impossible for these types of trials.

RCTs for non-drug therapies also have limitations associated with patient recruitment and adherence due to their preference of treatment [3]. Patients who visit TCM hospitals seeking non-drug treatment are likely to prefer such therapy. This not only increases the difficulty of recruiting for RCTs (especially for the control group) but also may lead to a high dropout rate during the trial.

A partially randomized, patient preference (PRPP) trial has been recommended for use in trials with potential performance bias [4-6]. This model was first applied for evaluating the therapeutic effect of surgery as compared with drugs, in which blinding methods could not be used due to the obvious inconformity between intervention and control treatment. Currently, this type of trial is widely used in studies that assess the effectiveness of a non-drug treatment (such as surgery) [7-11]. Given the limitations of a classical RCT, the PRPP model may be more suitable for evaluating non-drug TCM therapies. To date, there is no report on such trials in China to assess non-drug TCM therapies. Thus, our study is aimed at exploring the feasibility of applying the PRPP model to appraise the therapeutic effect of two kinds of non-drug therapies, acupuncture and cupping, while accounting for patient preference.

For this PRPP trial, we have chosen fibromyalgia as the target disease for three reasons. First, as a disorder with nonspecific symptoms of chronic widespread musculoskeletal pain and stiffness [12,13], fibromyalgia appears to affect increasing numbers of people and has a detrimental impact on their quality of life [14]. Second, acupuncture has been widely used for treating this condition [15]. Third, for pain conditions, the primary outcome is usually defined as pain relief as measured by a pain intensity instrument, such as a visual analog scale, which is based on patients’ subjective reporting and may be affected by belief, expectation, or preference of treatment modality.

Many kinds of TCM non-drug modalities are used to treat fibromyalgia. Acupuncture appears to have the most benefit in improving the main symptoms of fibromyalgia compared with herbal remedies [16-20]; thus, it is often recommended as an alternative therapy for this disorder [21]. Cupping therapy is an ancient Chinese healing modality. After systematically searching and analyzing clinical studies published in the last 50 years that used cupping therapy as the main intervention, we found that 70 of 550 studies evaluated cupping therapy for pain conditions [22]. From these studies, it appears that cupping therapy is effective for pain reduction in general, but few studies looked at cupping therapy for fibromyalgia. Our report [23] on medicinal cupping for fibromyalgia found that, after cupping therapy, the visual analogue scale (VAS) scores of 30 participants were reduced by 52.3% from baseline and the number of tender points was 30.9% fewer than in baseline. In China, acupuncture and cupping therapy are commonly used in TCM hospitals for pain management, but there have been no trials comparing these two treatment modalities for fibromyalgia.

### Objectives

The objectives of this trial are to assess the feasibility of applying the PRPP trial model in evaluating the therapeutic effect of acupuncture versus cupping, and to observe and compare the efficacies of these two therapies for fibromyalgia.

## Methods

This protocol was registered at the U.S. National Institute of Health ClinicalTrials.gov (identifier: NCT01869712; http://clinicaltrials.gov/ct2/show/NCT01869712?term=NCT01869712&rank=1). The protocol was last updated on 15 October 2013.

### Study design

This will be a partially randomized patient preference (PRPP) trial with four parallel groups: randomized cupping therapy, non-randomized cupping therapy, randomized acupuncture, and non-randomized acupuncture. Outcome assessors and statisticians will be blinded (Figure 1).

**Figure 1 F1:**
[figure not shown]
Study flow chart.

In this study design, participants without preference to a treatment modality will be randomly divided into either the cupping or acupuncture group. Participants with strong preferences will be assigned to their modality of choice. The PRPP design not only enables comparisons between participants with and without a preference and an exploration of participant characteristics associated with preference, but also enables evaluation of total therapeutic effect of the two modalities, while accounting for participant preference.

#### Setting and recruitment

The study will take place at the outpatient department of acupuncture and moxibustion, Affiliated Dongfang Hospital, Beijing University of Chinese Medicine, China. Outpatients will be recruited. Recruitment advertising will be via posters and flyers distributed in the hospital and nearby communities, as well as through the Internet. To increase adherence and maintain retention during the trial, five complimentary sessions of acupuncture or cupping therapy will be provided for all included participants after the trial.

#### Estimate of sample size

The first aim of this trial will be to investigate the feasibility of applying the PRPP model to evaluate the therapeutic effect of TCM non-drug therapy. The primary outcomes will be participant adherence and satisfaction. As a feasibility study, there is no previous study that provides relative data for us to use to calculate sample size.

The second aim of this trial will be to observe the therapeutic effect of the two types of TCM non-drug therapies of acupuncture and cupping for fibromyalgia with an equivalent test hypothesis. For this objective, the outcome will be pain relief, which will be measured by the VAS. We have used G*Power (version 3.1.2) to calculate the sample size.The analysis of variance (ANOVA) repeated measures technique was used as the statistical method during sample size calculation and will also be used for data analysis. To estimate the effect of cupping, we used data from our previous study [22], in which cupping produced a decrease in pain of 12.78 (SD = 5.88) points on the 100-mm VAS. We also used data from a trial on acupuncture for fibromyalgia [24] to estimate changes in pain that might occur in the acupuncture group. This corresponded to an estimated effect size of .2875. Using a two-tailed test with an alpha rate of .05, this meant that 38 participants are required per group to achieve 80% statistical power. Thus, we will aim for a total of 76 participants in two groups. Allowing for a dropout of 15%, we will recruit a total of 100 participants.

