#### Statistical analysis

To evaluate the feasibility of the PRPP model, we will use the chi-square, Cochran-Mantel-Haenszel (CMH)-chi-square, or Fisher’s exact test (as appropriate) to compare patient adherence and satisfaction toward treatment between groups and qualitative research methods to analyze patient and practitioner attitudes.

To assess the therapeutic effect of acupuncture and cupping therapy for fibromyalgia, we will use the chi-square, CMH-chi-square, or Fisher’s exact test (as appropriate) to compare baseline characteristics for categorical data. Analysis of variance (normal distribution) or non-parametric tests (skewed distribution) will compare baseline characteristics for continuous data. Analysis of primary outcomes will involve contrast analysis in which cupping therapy will be compared with acupuncture. This will indicate whether or not cupping and acupuncture differ in efficacy. This analysis will be conducted using repeat measurements in which outcomes will be compared at each follow-up, controlling for baseline scores. Intention-to-treat analysis[31] will be used in which missing data will be supplemented using the value that was assessed at the prior session (for example, if participant drops out at treatment session 6, then all outcome data would be noted as values at session 5). All calculations will be performed using SPSS for Windows (version 17.0, Chicago, Illinois), and *P*-values under .05 will be considered significant.

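### The efficacy aim is worded as equivalence, but the sample size and analysis are for a test of difference, with no margin, so the stated 80% is not power for the stated hypothesis

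*Protocol article*

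**What the plan says.** All references are to the protocol article.

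- **Estimate of sample size, hypothesis.** The second aim is to observe the therapeutic effect of "acupuncture and cupping for fibromyalgia with an equivalent test hypothesis". The endpoint is named next: "For this objective, the outcome will be pain relief, which will be measured by the VAS".
- **Estimate of sample size, calculation.** The expected changes come from two earlier studies. For the first, "cupping produced a decrease in pain of 12.78 (SD = 5.88) points on the 100-mm VAS". The article then says: "This corresponded to an estimated effect size of .2875". The group size is derived from that figure, for 80% power and 76 in total: "Using a two-tailed test with an alpha rate of .05, this meant that 38 participants are required per group". On method, the ANOVA "repeated measures technique was used as the statistical method during sample size calculation and will also be used for data analysis".
- **Statistical analysis.** Cupping is contrasted with acupuncture by repeated measures, controlling for baseline. "This will indicate whether or not cupping and acupuncture differ in efficacy". The only decision rule is that P-values under .05 count as significant.
- **Objectives.** The efficacy objective is to observe and compare the two therapies. Equivalence is not mentioned.

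No section gives an equivalence margin, a pair of one-sided tests or a confidence-interval criterion.

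**The concern.** An equivalence hypothesis needs a margin, and it is supported only when the data exclude differences larger than that margin. A two-sided test of difference takes equality as its null hypothesis, so failing to reject it is not evidence that the therapies are alike. Here the stated hypothesis is of the first kind, while the calculation and analysis are of the second.

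Two things follow. The 80% figure does not describe the chance of establishing what the sentence before it sets out to establish. And because the plan gives no other route to a conclusion about equivalence, a report could take P>.05 as support for it. That outcome becomes more likely as the trial gets smaller or noisier.

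**Working it through.** **1. Reproduce the plan's figure.** From the sample-size section: effect size .2875, two groups, two-tailed alpha .05, power 80%, repeated-measures ANOVA in G*Power. The article states neither the number of measurements m nor their correlation ρ, so both are assumed here. I read .2875 as Cohen's f and use the between-groups F test:

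λ = f²·N·m / [1 + (m − 1)ρ], with 1 and N − 2 degrees of freedom.

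| m | ρ | smallest even N for 80% | λ at that N |
|---|---|---|---|
| 2 | .5 | 74 | .2875² × 74 × 2 / 1.5 = 8.16 |
| 4 | .7 | 76 | .2875² × 76 × 4 / 3.1 = 8.11 |
| 5 | .7 | 76 | .2875² × 76 × 5 / 3.8 = 8.27 |
| 1 | – | 98 | .2875² × 98 = 8.10 |

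The stated 76 is recovered under plausible settings. Reading .2875 as Cohen's d at one measurement would need about 380 in total, so f is the likelier reading. No margin enters the calculation. It is a pure difference-test sample size, and the 80% is the chance of rejecting equality if the assumed difference is real.

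**2. Chance of a non-significant result when the therapies do differ.** Take a true difference of 10 mm on the 100-mm VAS (illustrative), one time point and a two-sample t-test, with non-centrality (10/SD)·√(n/2). For n = 38 and SD 20 this is 0.5 × √19 = 2.18.

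| SD (mm) | source | P>.05, 38 per group |
|---|---|---|
| 5.88 | article | about 0% |
| 10 | assumed | 1% |
| 15 | assumed | 18% |
| 20 | assumed | 42% |
| 25 | assumed | 59% |

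With the mean of four measurements at ρ = .7, the variance is multiplied by (1 + 3 × .7)/4 = 0.775. The last three figures then fall to 10%, 31% and 50%.

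**3. Power to show equivalence with the planned numbers.** This uses two one-sided 5% t-tests (90% CI inside the margin), true difference 0, 38 per group and one time point. The margin of ±10 mm is only an illustration, since the article gives none.

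| SD (mm) | power for ±10 mm |
|---|---|
| 5.88 | about 100% |
| 10 | 99% |
| 15 | 78% |
| 20 | 39% |
| 25 | 8% |

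The margin matters as much as the SD. At SD 5.88, a normal approximation gives power of 0% for ±2 mm, 44% for ±3 mm and 96% for ±5 mm. So even on the article's own SD, the power for equivalence cannot be stated until a margin is fixed. None of these figures is the plan's 80%.

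**The case against.** **The equivalence wording may be a slip.** Within the efficacy plan it appears once, in an awkward phrase that could be loose English for a null hypothesis of equality. The objectives, the calculation and the analysis section all describe a comparison for difference. On that reading the design is coherent and one phrase is wrong. This is fair, and it is why the preferred fix is to remove the phrase. It does not remove the contradiction, because a reader of the sample-size section is told that the trial tests equivalence with 80% power.

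**The misuse of P>.05 is not stated.** A reader might infer that the plan will declare equivalence whenever P>.05. The documents do not say so. They say only that P-values under .05 are significant and that the contrast shows whether the therapies differ. The harm is therefore a risk, not a planned step.

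**The large error rates rest on assumed SDs.** A reader who looked only at SDs of 15 to 25 might conclude that a missed 10 mm difference is likely. The only VAS SD in the article is 5.88, where that chance is about 0% and a ±10 mm margin would be met almost surely. That figure comes from one cupping study and may be optimistic for this trial, but the article gives no basis for a larger one. The planned repeated-measures analysis would also do somewhat better than a single time point.

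**Efficacy is the second aim.** Adherence, satisfaction and practitioner attitude are the primary outcomes, and VAS is listed as secondary. The point therefore does not affect the feasibility conclusions. Against that, efficacy is the only aim with a sample-size calculation, so it supplies the 76 behind the planned 100.

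**A margin could be left to an analysis plan.** Its details could. But the hypothesis and the sample size are both fixed here and disagree, and adding a margin later would not turn this 80% into power for equivalence.

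**Conclusion.** The contradiction stands. The efficacy aim is stated as equivalence, while the sample size and the analysis are for a difference, with no margin or confidence-interval rule. The stated 80% is power to detect a difference. That conclusion needs no assumption about the SD; reproducing 76 needs only assumed values for the number of measurements and their correlation.

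A non-significant result could be misread as supporting equivalence. For a true 10 mm difference, one time point and 38 per group, the chance of such a result runs from about 0% at the article's SD to 59% at an assumed SD of 25. The documents do not support saying that this misreading is planned, nor that the trial is necessarily too small for equivalence: that depends on a margin and an SD that are not settled. Because VAS is a secondary outcome and a wording change resolves the matter, this should be fixed but does not threaten the trial's primary purpose.

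**What to change.** **Preferred.** In the sample-size section, delete the words that make the hypothesis one of equivalence, which brings it into line with the objectives. Label the 80% as power to detect a difference. In the statistical analysis section, state that the cupping-minus-acupuncture difference in VAS will be reported with a 95% CI and that P>.05 will not be taken as equivalence. This costs a few sentences and no patients.

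**If equivalence is really intended.** Fix and justify a VAS margin before database lock. Conclude equivalence only if the 90% CI for the difference lies wholly inside it. Replace the 80% with the power that the planned numbers give for that margin, with the assumed SD stated. This also needs no more patients, provided the team accepts that the restated power may be low. Aiming for 80% power could need more: at one time point and one-sided .05, a normal approximation gives 52 per group for a margin of 0.575 SD and 69 for 0.5 SD.

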#### Generation of the allocation sequence of randomization

Fifty patients who have no preference for either of the two therapies (acupuncture or cupping) will be randomly allocated to either the cupping or the acupuncture group. We will use SAS 8.0 software to create the sequence of randomization [25], total number of cases is 50, number of groups is 2, distribution ratio of the two groups is 1:1.

This sequence of randomization will be contained in opaque sealed envelopes and kept by researcher A, who will be contacted by each practitioner to provide the allocation.

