#### Approach for cases of dropout/lost to follow-up/need to screen

1. Dropout cases will be defined as enrolled participants who miss a treatment session or refuse treatment as scheduled. We will consider at least 80% of the planned recruitment (40 cases in each group) to provide sufficient data for analysis.

2. Lost to follow-up will be defined as participants who complete all treatments, but cannot be contacted for follow-up.

3. Need to screen will be defined as enrolled participants who have serious adverse events during the trial. Researchers will be expected to halt treatment immediately and note the reason for the adverse event.

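### The 80% power at 38 per group can only describe a pooled, partly self-selected comparison; the randomised comparison (25 per arm) has about 54–62%, and the step from 76 to 100 is not a 15% dropout allowance

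*Protocol article*

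**What the plan says.** All references are to the protocol article.

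- **Estimate of sample size.** Pain on the VAS is the second aim, and the only one with a calculation. The method is given as "The analysis of variance (ANOVA) repeated measures technique was used as the statistical method during sample size calculation", with "This corresponded to an estimated effect size of .2875" and "Using a two-tailed test with an alpha rate of .05". The result is "this meant that 38 participants are required per group to achieve 80% statistical power", followed by "Thus, we will aim for a total of 76 participants in two groups" and "Allowing for a dropout of 15%, we will recruit a total of 100 participants".
- **Generation of the allocation sequence of randomization.** The list is fixed as "total number of cases is 50, number of groups is 2, distribution ratio of the two groups is 1:1".
- **Abstract, Methods.** The other 50 participants have a strong preference and receive the therapy they choose.
- **Study design.** There are four parallel groups: randomised and non-randomised, for each therapy.
- **Approach for cases of dropout/lost to follow-up/need to screen.** The data-sufficiency threshold is "at least 80% of the planned recruitment (40 cases in each group) to provide sufficient data for analysis".
- **Statistical analysis.** Cupping is contrasted with acupuncture by repeated measures. The section does not say whether this is done in randomised patients, preference patients or both. Missing values are replaced by the previous session's value.

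**The concern.** The power calculation is for two groups, the design has four, and neither randomised arm reaches the required size. A reader who takes the 80% to cover the acupuncture-versus-cupping contrast that randomisation protects would be wrong, and the sample-size section gives no warning.

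Two misuses follow. The section describes its hypothesis as one of equivalence, so a non-significant result in 25 versus 25 could be read as evidence that the therapies are equivalent, when it may only reflect low power. Alternatively, the efficacy conclusion could move to the pooled contrast without the reader being told that half of those patients selected their own treatment. Preference and expectation are the very influences on subjective pain scores that the Background gives as the reason for this design.

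The step from 76 to 100 is a smaller matter, but it is a stated derivation that does not follow from its stated inputs.

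**Working it through.** **Inputs.** From Estimate of sample size: two-sided alpha 0.05, power 80%, effect size 0.2875, 38 per group (76), dropout 15%, 100 recruited. From the allocation section: 50 randomised 1:1, so 25 per arm. Not stated: the type of effect size, the number of measurements m, and their correlation ρ.

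**1. Reproducing the 38.** Read 0.2875 as Cohen's f and use the between-group test in a repeated-measures ANOVA:

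λ = f² · N · m / (1 + (m − 1)ρ), with 1 and N − 2 degrees of freedom.

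For m = 4 and ρ = 0.7 (assumed) at N = 76: λ = 0.08266 × 76 × 4 / 3.1 = 8.11, power 80.2%. Smallest even N for 80%:

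| m | ρ | total N |
|---|---|---|
| 4 or 5 | 0.7 | 76 |
| 6 or 7 | 0.7 | 74 |
| 2 | 0.5 | 74 |
| 7 | 0.5 | 58 |
| 1 | – | 98 |

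So 38 per group is attainable under plausible settings, but the article does not give enough to confirm it.

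**2. Power of the randomised comparison.** To avoid guessing m and ρ, accept the plan's 80% at N = 76. With 1 and 74 degrees of freedom this requires λ = 8.06. For the same effect, m and ρ, λ is proportional to N:

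- 50 analysed (25 per arm): λ = 8.06 × 50/76 = 5.30, df 1 and 48, power **61.6%**.
- About 21 per arm after 15% loss (25 × 0.85 = 21.25; N = 42): λ = 8.06 × 42/76 = 4.45, df 1 and 40, power **54.0%**.

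**3. Power of the pooled comparison.** With 100 × 0.85 = 85 evaluable and an even preference split: λ = 8.06 × 85/76 = 9.01, df 1 and 83, power **84.3%**.

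**4. Sensitivity of step 2.**

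- If the calculation was for a group-by-time interaction with 4 to 7 measurements, the same calibration gives 58–60% at N = 50 and 50–51% at N = 42.
- If 38 is not taken as correct and f = 0.2875 is used directly, 25 per arm has about 51% with one measurement and 75% with m = 7 and ρ = 0.5.

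**5. Dropout step.**

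- 76 / (1 − 0.15) = 89.4, so 90.
- The common shortcut 76 × 1.15 = 87.4 gives 88.
- 1 − 76/100 = 24%, the allowance that 100 actually makes.

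**6. The threshold of 40 per group.** 40 is 80% of 50, so the groups meant are whole modalities. Each has 25 randomised patients, so each needs at least 40 − 25 = 15 of the 50 preference patients even with no dropout. With X binomial (50, p), the chance that either modality gets fewer than 15 is:

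| assumed preference split | chance 40 is out of reach |
|---|---|
| 50:50 | 0.3% |
| 40:60 | 5% |
| 35:65 | 19% |
| 30:70 | 45% |

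The documents give no expected split; these are assumptions.

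**The case against.** The strongest reply is that the plan never claims 80% power for the randomised arms. It sizes two groups, recruits 100, and sets a threshold of 40 as 80% of each group, which only makes sense for modalities of 50 with randomised and preference patients together. The Study design section also names a total effect of the two modalities, accounting for preference, as a purpose of the design. This stands. A reader might infer that the plan advertises a power it does not have; the documents do not support that. What remains is that the sample-size section does not say its 80% is for a pooled, partly self-selected contrast.

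Other replies also stand, in whole or in part:

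- **Pain is secondary.** Adherence, satisfaction and practitioner attitude are the primary outcomes. This lowers the weight. It does not remove the point: comparing efficacy is a stated objective, and the Statistical analysis section refers to primary outcomes when it describes the efficacy contrast.
- **Dropouts are kept.** Earlier values are carried forward, so the analysed number stays nearer 50. The 54% therefore applies only if 15% contribute no data, and 62% is the figure if all 50 are analysed.
- **Over-recruitment is harmless.** Recruiting 100 where 90 would do costs no power. The error is in the derivation only.
- **There are not three dropout rates.** A reader might set 15%, 24% and the 80% threshold side by side as three conflicting assumptions. The 80% is a rule for sufficient data, not a forecast of dropout, and 40 exceeds the required 38.
- **The threshold is not shown to be unreachable.** With preferences near even it is almost sure to be reachable before dropout. The risk is material only for lopsided splits.

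**Conclusion.** The point holds in this form. The 38 per group behind the 80% cannot be met by the 25 randomised per arm, and the section does not say that the figure relies on pooling with patients who chose their therapy. For the same difference, the randomised comparison has about 62% power with all 50 analysed and about 54% with 15% contributing no data, against about 84% for the pooled contrast with 85 evaluable and an even split.

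These figures assume that the plan's 80% at 76 is right and that the test is a between-group F-test for a difference. They are not power for equivalence. The sensitivity checks move them but do not bring the randomised comparison to 80% in any setting tried.

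The dropout sentence is wrong by simple arithmetic, without any assumption: 15% gives 90, and 100 allows 24%.

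Severity is moderate: pain is a secondary outcome of a feasibility trial, and the fault lies in what is stated, not in the number recruited.

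**What to change.** 1. In Estimate of sample size, state that the 80% applies to the pooled comparison of modalities, which includes self-selected patients and is not protected by randomisation.
2. Add there that the randomised comparison (25 per arm) has roughly 54–62% power for the same difference, conditional on the 38-per-group calculation and on a difference test. State that it will be reported as an estimate with 95% CI, and that non-significance will not be read as equivalence.
3. Correct the dropout sentence: either 15% dropout, giving 90, or 100 recruited, allowing for 24%.
4. In the dropout section, restate the threshold of 40 as applying to pooled modality groups, and note that reaching it depends on a preference split the trial does not control.

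The cost is a few restated sentences. No patients, visits or analyses are added.
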